## Abstract

**Background:**

Among the most burdensome clinical conditions occurring in older persons, respiratory infections are particularly relevant. In fact, the onset of pneumonias is associated with a significant worsening of the individual’s global health status and significant increase of healthcare costs. The clinical and economical negative consequences of pneumonia may be particularly evident among the frailest groups of elders, in particular those living in nursing home. Nevertheless, specific research on incidence and economical effects of pneumonia in nursing homes residents is still scarce. In the present article, we present the rationale, the design and the methods of the “Incidence of pNeumonia and related ConseqUences in nursing home Resident (INCUR) study, specifically aimed at filling some of the gaps currently present in the field.

**Methods/design:**

INCUR is an observational longitudinal study recruiting 800 residents across 13 randomly selected nursing homes in France. Multidimensional evaluations of participants are conducted at the baseline, mid-term (at 6 months), and end of the study (at 12 months) visits in order to measure and follow-up their physical function, nutrition, cognition, depression, quality of life, and healthcare costs. Incident pneumonia as well as the onset/recurrence of other major health-related events are monitored during the study follow-up.

**Discussion:**

The INCUR study will provide valuable information about older persons living in nursing homes. Results from INCUR study may constitute the basis for the development of future preventive campaigns against pneumonia and its consequences.

## Background

Over the past years, the number and prevalence of older persons in industrialized countries have steadily grown [1]. Consistently, the number of people living in nursing home is also increased and is expected to further rise. To date, in the United States, there are about ~16,100 nursing homes with ~1.5 million residents for ~314 million inhabitants [2]. The projected national cost of nursing home for 2000 exceeded $140 billion, but may exceed $700 billion by 2030 [3]. In France, about 700,000 persons (representing 1.2% of the national population) [4] currently live in ~10 000 nursing homes [2]. Unfortunately, research in nursing homes is still scarce. It has been estimated that only 2% of studies in the geriatrics are carried out in this specific setting [4] which is not only characterized by a steady expansion, but is also particularly burdensome for the healthcare system.

The lack of research in nursing home may be easily explained by the complexity and heterogeneity of the older persons living in this setting and their limited access to study protocols [5,6]. The vast majority of nursing home residents is characterized by the most dramatic results of the pathophysiological modifications and chronic conditions experienced and accumulated during the entire life course. The complexity of nursing home residents is due to the high comorbidity [7,8], the frequent polypharmacy (especially including psychotropic drugs [9]) [10] the presence of major geriatric syndromes (e.g., falls [11]), and the general poor health status (e.g., malnutrition [12]). In particular, it cannot be ignored that the high prevalence of physical disability in this population. Fried and colleagues [13] calculated that although older persons represent only the 19% of the entire United States population, their healthcare needs demand almost half of the public health budget. Such economical estimation was largely influenced by the presence of disabling conditions. Both the increasing number of nursing home residents and the heavy burden they impose to public health expenditures make the study of this population a research priority in order to design and hopefully implement future *ad hoc* preventive and therapeutical interventions.

Any acute illness (in particular, respiratory conditions [14]) negatively affects physical function of older persons [15]. Therefore, the prevention of physical disability (the primary aim of geriatric medicine) may necessarily imply the need to consider preventive interventions targeting specific acute clinical conditions. The implementation of preventive campaigns is important for the subject (who may reduce the own risk of experiencing the disease) as well as for the healthcare system (which may significantly save resources).

It is possible that the frail older persons living in nursing homes may be specially amenable of beneficiating from preventive interventions and protocols [16]. In fact, the high risk of health-related events and complications to which this population is exposed may reduce the cost-effectiveness ratio of a preventive protocol. Interestingly, the same protocol may differently be unfeasible in community-dwelling subjects because a too large number of persons should receive the intervention in order to gain significant benefits. Moreover, a limited improvement (or even the avoidance of health loss) in a frail older person may have relevant effects for public health, given the exponential relationship between healthcare costs and physical function [13].

Although the incidence of infectious diseases has been largely decreasing in young and adult persons in Western Countries over the last century, similar trends have not been reported in older persons [17-20]. The atypical presentations of infections at advanced age (including lack of fever, behavioral changes, confusion) are responsible for diagnostic difficulties resulting in incorrect therapeutical prescriptions. For example, it has been reported that a significant proportion of antibiotics use is not justified or not adequately prescribed in nursing homes [21,22]. The erroneous use of antibiotics contributes not only to generate bacterial resistances, but also increases direct and indirect costs [21,23].

Most of the observational studies estimating the incidence and effects of infectious diseases has been performed at the community level. Limited evidence on this topic is currently available in nursing homes and long-term care facilities which generally host older persons with higher morbidity and increased mortality risk [20,24]. Moreover, as suggested by the large variations of prevalence and incidence rates available in literature (mainly due to differences in methodological approaches, intensity of surveillance, case mix, and facility administration [25]), data from these healthcare settings are far to be definitive. Just to provide few examples about the relevance of the (currently underestimated) phenomenon in nursing home: it has been calculated that the prevalence of infections (i.e., respiratory, cutaneous, and urinary) in institutionalized older persons may range from 1.6% to 32%, and the overall incidence rates vary from 1.8 to 13.5 infections per 1,000 residents-year [26]. These figures are at least 10-fold higher than those reported in community-dwelling older persons [27]. In this context, the respiratory system is one of the most frequently affected sites for infections. The incidence of nursing home-acquired pneumonia in the United States varies between 0.3 and 2.3 episodes per 1,000 resident-days [25]. In a recent paper, Ahmed and colleagues [28] explored the hospitalization events occurring among nursing home residents in the United States, finding that pneumonia was the leading primary discharge diagnosis from the hospital (6%) and a major predictor of in-hospital mortality.

The purpose of the present article is to present the design and methodological approach of the “Incidence of pNeumonia and related ConseqUences in nursing home Resident” (INCUR) study. INCUR is an observational longitudinal cohort study aimed at estimating the incidence and economical effects of pneumonia in older persons living in nursing homes (i.e., *Etablissement d’Hébergement pour Personnes Agées Dépendantes*, EHPAD) in France.

### The INCUR study

#### Hypotheses and objectives

The INCUR project is specifically aimed at retrieving data from routine clinical practice in order to estimate the incidence of pneumonia events in older persons living in a sample of French nursing homes. Moreover, INCUR is designed to estimate the clinical and economical consequences of pneumonia events by measuring the subsequent access to medical procedures and resources. More in details, the following hypotheses have driven the rationale and conception of the INCUR project:

Primary hypotheses:

a. Pneumonia is a clinical condition frequently complicating the nursing home stay of older persons;

Secondary hypotheses:

a. The onset of a pneumonia event in institutionalized older residents is associated with higher healthcare costs;

b. Incident pneumonia events are associated with an increased risk of mortality in older persons living in nursing home;

c. The onset of a pneumonia event is responsible for a significant worsening of the physical function of nursing home residents;

Tertiary hypotheses:

a. Specific variables at patient- and nursing home-level may predict the severity of the pneumonia-related functional loss;

b. Nursing home residents dying due to pneumonia produce a significantly higher burden in terms of healthcare costs compared to nursing home residents dying for other causes.

Therefore, the INCUR project will pursue the following aims:

Primary aims:

a. To estimate the incidence of pneumonia events in a sample of older nursing home persons over a period of 12 months;

Secondary aims:

a. To compare the healthcare costs of nursing home older persons experiencing a pneumonia event versus those who will not over a period of 12 months;

b. To calculate the mortality risk in a sample of older residents living in nursing home according to the presence/absence of a pneumonia event occurred during a follow-up period of 12 months;

c. To measure the physical function modifications experienced by a sample of nursing home residents according to the presence/absence of a pneumonia event occurred during a follow-up period of 12 months;

Tertiary aims:

a. To identify sociodemographic, clinical, and biological characteristics of nursing home older residents, as well as environmental and organizational factors of their own hosting institution, which are associated with a higher degree of functional loss following a pneumonia event;

b. To explore whether mortality due to pneumonia is associated with higher healthcare costs compared to death events due to non-respiratory causes in nursing home older residents.

## Methods/design

For the INCUR project, we recruited 800 residents of 13 nursing homes randomly selected in the Midi-Pyrénées region of France. In particular, nursing homes of the region were consecutively and randomly invited at participating in INCUR. After each nursing home accepted to be involved in the study, all its residents (according to their eligibility for INCUR) were assessed by the study personnel. The recruitment was conducted up to the reaching of the final sample of 800 participants according to the predefined sample size analyses (see specific paragraph). All the nursing homes were part of a national network of institutions representative of this healthcare in France [4]. To be part of the project, the director, the coordinating physician, and the responsible for the nursing of each institution signed a formal agreement and letter of support.

The main inclusion and exclusion criteria were the constituted by the score obtained by the participant at the *Autonomie Gérontologie - Groupes Iso-Ressources* (AGGIR) scale (Table 1). This scale allows to homogeneously generate six *Groupes Iso-Ressources* (GIR) at the French national level. The resulting GIR expresses the global functional capacity of the person and drives decisions about the provision of social support from public healthcare system. Subjects with severe disability are excluded from INCUR on the basis of the worst GIR group (i.e., 1). The reason for such exclusion resides in the impossibility to determine in these patients the weight of functional loss due to a pneumonia event (primary aim d). Similarly, residents with no sign of functional impairment at the AGGIR scale (that is having the maximum GIR score of 6) are excluded due to the incapacity to perceive possible functional improvement over the follow-up.

**Table 1 T1:** Inclusion and exclusion criteria of the INCUR study

*Inclusion criteria*	*-* Residents aged 60 years and older
	*- Groupes Iso-Ressources* (GIR) ranging between 2 (included) and 5 (included). This is the French administrative tool used to rate the ability of the person to be independent; it ranges from 6 (fully independent) to 1 (fully dependent, bed-ridden)
*Exclusion criteria*	- Residents living in the participating nursing homes for less than 30 days since the baseline study visit
	- Refusal of the patient and/or the family to participate at the INCUR project

Each eligible participant will be followed-up for 12 months with a total of three clinical assessments: at baseline, 6 months (mid-term visit), and 12 months (close-out visit). The timeline of the INCUR project is depicted in Figure 1. Recruitment of participants and baseline visits began in February 2012 and ended in July 2012, after a preliminary organization phase (for coordinating activities of researcher with the participating nursing homes). The mid-term visit of participants (after 6 months of follow-up) is currently ongoing.

**Figure 1 F1:**
[figure not shown]
The timeline of the INCUR project.

The INCUR visits are conducted by research staff specifically trained at the Gérontopôle of Toulouse. The evaluations will be conducted using multiple scales, questionnaires and tests based on the Geriatric Minimum Data Set (GMDS) [29], thus allowing a comprehensive assessment of participants. The GMDS is a package of assessment tools designed by a multidisciplinary task force group (i.e., the Gerontonet) [30], aimed at evaluating the different areas of the person’s health, including physical function, nutrition, cognition, depression, quality of life. As shown in Table 2, these include: ADL [31], Instrumental ADL (IADL) [32], European Quality of Life (EuroQoL) instrument [33], frailty phenotype proposed by Fried and colleagues [34], Abbreviated Mental Test [35], 15-item Geriatric Depression Scale [36], Mini Nutritional Assessment [37]. The GMDS instrument was originally conceived to promote the translation of routinely collected clinical parameters into research data. Therefore, consistently with the descriptive nature of the INCUR project, the items collected will be primarily retrieved from the medical charts of the participants (if present). Missing data will be completed by specific evaluations of the INCUR study staff.

**Table 2 T2:** Main areas investigated and related instruments adopted in the INCUR project

**Area**	**INCUR assessment**
Sociodemographics	
Body composition	Anthropometric measures
Anamnesis/Comorbidity	Current diseases
Medications	
Vaccinations	Influenza and pneumococcal vaccine
Cognition	Abbreviated Mental Test
	Geriatrics Depression Scale
Quality of life	Euro-QoL 5D
Pain	Pain Visuo-Analogic Scale
Functional Status	Activities of Daily Living
	Instrumental Activities of Daily Living
	Short Physical Performance Battery
	Hand grip strength
Nutrition	Mini Nutritional Assessment
Healthcare cost	Data from the *Caisse Primaire d’Assurance Maladie*
Follow-up	Intercurrent diseases
	Therapy modifications
	Hospitalization events
	Death events and causes of death

The same standardized multidimensional assessment performed at the baseline will then be repeated at the 6- and 12-month follow-up visits. Additionally, the follow-up visits will be specifically focused at identifying the onset of major health-related events (in particular pneumonia) occurred during the previous 6 months of follow-up. In particular, the study staff will retrieve information about major intercurrent illnesses, emergency room admissions, hospitalizations, and death events (including causes) from patient's medical records and charts, the nursing home personnel, and the proxies of the participant. Moreover, in between the follow-up visits, regular contacts between the study staff and the nursing homes personnel will be maintained in order to facilitate and improve the identification of the health-related events experienced by the INCUR participants.

To design and develop the INCUR study, the principles of the Declaration of Helsinki have been followed and ethical standards complied. The Ethics Committee of the Centre Hospitalier Universitaire de Toulouse and the Consultative Committee for the Treatment of Research Information on Health (CNIL) approved the entire study protocol. The Ethics Committee waived the need for written informed consent from the participants given the epidemiological nature of the research within the domain of current clinical practices. Therefore, participants are not required to provide a written informed to the study, but all participants receive written information about the ongoing research (including its objectives and procedures) by the study investigators. Residents are then free to exclude their data from the collection or analysis at any time. In case of residents with cognitive impairment or unable to understand the research protocol, proxies are informed.

### Pneumonia

From a clinical standpoint of view, it is difficult to obtain a clear and definitive diagnosis of pneumonia in the nursing homes population beacause of the multitude of comorbidities (e.g., heart failure, chronic obstructive pulmonary disease, pulmonary fibrosis) often altering the manifestation of the respiratory infection. For example, cough is often absent (even in more than 50% of the cases), pulmonary crackles are rare, and the only reliable criterion remains the increased respiratory rate. Such difficulties combined with the limited access to complementary biological or imaging exams lead to unreliable estimates for the diagnosis of pneumonia in the nursing homes setting. To improve the diagnostic definition of pneumonia, the *Observatoire du Risque Infectieux en Gériatrie* (ORIG) [38] recently published specific criteria refining those previously proposed by McGeer and colleagues [39]. The ORIG criteria described by Rothan-Tondeur and colleagues [38] are specifically adapted for use in the nursing homes, taking into account the diagnostic difficulties characterizing this clinical setting. Thus, the ORIG definition of a pneumonia event mirrors the one based on the McGeer and colleagues’ algorithm [39], but replace the most invasive and complex endoscopic and microbiological criteria with the physician’s clinical judgement.

In the INCUR study, consistently with the ORIG proposition, we will identify pneumonia events on the basis of the following two criteria:

1. Presence of at least two of the following signs/symptoms:

a. Worsening or onset of cough, purulent sputum, or specific signs at the auscultation,

a. Fever (≥38°C),

a. Thoracic pain,

a. High respiratory rate (≥25 breaths per minute),

a. Mental confusion or worsening of physical disability, and

2. Clinical evidence documented by a physician of crackles at the thoracic auscultation.

It has been reported that the probable cases identified using the ORIG definition are about 3.5-fold higher than the definitive cases of pneumonia identified using the McGeer and colleagues criteria [39]. Surely, this latter definition is more accurate and completely based on objective data. However, its difficult clinical implementation (especially in the nursing homes) and the large difference in the identified cases of pneumonia (compared to the ORIG definition) may be responsible for a likely underestimation of the phenomenon and an inadequate capacity to be adapted to such healthcare setting.

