### Healthcare costs

To address the second aim of the present project related to the healthcare costs of pneumonia events in older persons living in nursing homes, the INCUR project will obtain specific data from the *Caisse Primaire d’Assurance Maladie* (i.e., the French national healthcare insurance system). In particular, the study coordinators will receive the direct costs that the healthcare system will sustain for each INCUR participant during the study period. Such figures will include total and detailed expenditures (including performed medical procedures, medications consumption, access to specific healthcare services…). As mentioned, specific parameters acting as surrogated measures of healthcare expenditures will also be directly retrieved during the INCUR clinical visits from the participants’ medical records and charts by the INCUR personnel. In particular, we will evaluate the following parameters: number and length of hospitalization events, number of major medical procedures (including admission and length of stay in Intensive Care Unit, Orotracheal intubation, mechanical ventilation), and transition to worse GIR classes. Although these (mainly clinical) parameters may not provide the exact estimation of the costs sustained by the healthcare system for the patient, they still represent reliable markers of the economical weight of the case. Moreover, since all these procedures and events have direct and negative influences on the older patient’s quality of life and functional status, their significance goes well beyond a mere financial evaluation. The collaboration with the CNAM will provide us a detailed estimation of healthcare costs charged to the public healthcare system for the management of INCUR participants. Nevertheless, the main limitation of INCUR in this context is represented by the impossibility to detect and measure costs directly sustained by the participant (and his/her family) and the impact of caregivers’ time on societal aspects.

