c. When a pneumonia event will occur, physical function information collected after its onset will be compared to those previously recorded. The difference in physical function measured before and after the pneumonia event will be adjusted for the days between the event onset and the following physical function assessment. This analytical approach will allow to take into account the negative influence that the presence of a (sub)acute phase of the respiratory process may exert on physical function if the event will occur close to the evaluation. Mixed effects analysis of covariance models will also be performed to evaluate physical function modifications over time between patients who experienced a pneumonia event versus those who did not. If statistical power will be sufficient, stratified analyses will also be performed according to the severity of the pneumonia event (e.g., events requiring hospitalization versus those who did not).

For the present analyses, the sum of the results from the three SPPB categorized tests (ranging from 0 [worst physical performance] to 12 [best physical performance]) as well as the crude timed results obtained from each single assessment (in seconds) will be used for the analyses. This will allow to evaluate whether the pneumonia event will differently affect specific components of physical performance (i.e., balance, muscle strength, or gait/coordination).

Tertiary aims:

a. Chi-square and t-test analyses will be performed to describe the study population for main sociodemographic, behavioral, and clinical characteristics according to the presence/absence of a pneumonia event occurred during the INCUR project follow-up. Mann-Whitney U statistics will be used for non-normally distributed continuous variables. Normalization through log-transformation will be used for non-normally distributed study variables. Subsequent unadjusted and adjusted Cox proportional hazard models will be analyzed to identify patients’ characteristics that are able to significantly predict pneumonia events (dependent variable of interest). Among the covariates, age, gender, race, and preexisting respiratory conditions will always be considered as potential confounders. Age, gender, and race interactions will be tested for the studied relationships by adding specific interaction terms into the models. If possible, stratified analyses will be performed whereas significant interactions will be obtained.

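### Worsening disability is part of one qualifying sign for pneumonia, so exposure and outcome partly overlap when the study asks whether pneumonia worsens physical function

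*Protocol article*

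**What the plan says.** The section Pneumonia sets two criteria, and both must be met.

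- Criterion 1: "Presence of at least two of the following signs/symptoms". Five items follow. The first is "Worsening or onset of cough, purulent sputum, or specific signs at the auscultation"; three others are fever, thoracic pain and a high respiratory rate; the last is "Mental confusion or worsening of physical disability".
- Criterion 2: "Clinical evidence documented by a physician of crackles at the thoracic auscultation".

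Under Hypotheses and objectives, secondary hypothesis c is "The onset of a pneumonia event is responsible for a significant worsening of the physical function of nursing home residents". The matching aim is "To measure the physical function modifications experienced by a sample of nursing home residents according to the presence/absence of a pneumonia event". Tertiary aim a, as worded there, seeks characteristics associated with greater functional loss after an event.

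The Analysis plan for secondary aim c uses the same case label twice. It compares function before and after onset, adjusted for the days from onset to the next assessment. It also fits mixed-effects models to "evaluate physical function modifications over time between patients who experienced a pneumonia event versus those who did not".

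Physical function measures lists ADL, IADL, SPPB, grip strength and GIR. Function is assessed at baseline, 6 and 12 months, with items taken from the medical charts first. Healthcare costs also names "transition to worse GIR classes" as a surrogate cost marker. The article does not mention the overlap between the case definition and the functional outcome.

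**The concern.** An exposure that is partly defined by the outcome selects residents who decline into the exposed group. Suppose a resident has crackles from another cause and one other sign short of the threshold. If that resident also loses function, the episode becomes pneumonia; if not, it does not. Comparing function between cases and non-cases then shows some excess decline in cases even if pneumonia has no effect on function.

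The stated adjustment for days since onset deals with measurements taken during the acute phase. It does not change who is labelled a case. The before value comes from an earlier visit, so decline that preceded the respiratory episode falls in the same interval as decline that followed it.

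What is at stake is the interpretation of hypothesis c. A positive finding could not be fully separated from the way cases were defined. Tertiary aim a is exposed too, because factors that predict decline in general may look like predictors of loss caused by pneumonia.

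**Working it through.** **The plan's own event counts.** The point rests on no stated figure, but the counts give scale. From Sample size analyses: 22 / 2,140 / 28 × 365 × 800 = 107.2 events. With 20% mortality and 40% fewer events over six months (a factor of 0.8 each), 107.2 × 0.8 × 0.8 = 68.6. Both reproduce.

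**Sign patterns.** Five yes/no items give 32 patterns; 32 − 1 − 5 = 26 have at least two signs. Of these, 15 include the confusion/disability item, and 4 reach two signs only because of it (that item plus exactly one of the other four). If the mandatory crackles also count as the first item, 15 patterns qualify, 8 include the confusion/disability item and 1 needs it. These are counts of patterns, not of events.

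**Share of events that need the disability part.** The article gives no sign frequencies. Assumptions, among episodes with crackles and with signs independent: fever 40%, high respiratory rate 40%, thoracic pain 10%, confusion 20%, recent functional decline δ = 10%, 20% or 30%. Let q be the share of cases that qualify only through disability.

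*Crackles also count as the first item.* The chance that fever, pain and high respiratory rate are all absent is 0.6 × 0.9 × 0.6 = 0.324. Then q = 0.324 × 0.8 × δ / [1 − 0.324 × 0.8 × (1 − δ)]. For δ = 20%: 0.0518 / 0.7926 = 6.5%.

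*First item present in 50%, independently of crackles.* The chance of exactly one of the other four signs is 0.162 + 0.108 + 0.018 + 0.108 = 0.396, and of two or more it is 0.442. Then q = 0.396 × 0.8 × δ / [0.442 + 0.396 × (1 − 0.8 × (1 − δ))]. For δ = 20%: 0.0634 / 0.5846 = 10.8%.

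| δ | q, crackles count as first item | q, first item in 50% |
|---|---|---|
| 10% | 3.4% | 5.7% |
| 20% | 6.5% | 10.8% |
| 30% | 9.5% | 15.4% |

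The share needing the whole item, confusion included, is higher (12% to 28% in simulation), but only the disability part overlaps the outcome. On the plan's worst case of 68.6 events, q of 3.4% to 15.4% is about 2 to 11 events.

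**Resulting bias with no true effect.** Let ρ be the chance that a decline is still present at the next visit. The proportion with decline at the visit is δρ in all crackle episodes and δρ + qρ(1 − δ) in cases. For δ = 20%, ρ = 50%:

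- Crackles count as first item: 0.100 + 0.065 × 0.5 × 0.8 = 12.6%.
- First item in 50%: 0.100 + 0.108 × 0.5 × 0.8 = 14.3%.

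A simulation gave the same two figures, and 10.0% in cases once the item was removed. The ratio is 1 + q(1 − δ)/δ, which runs from about 1.2 to 1.5 over the table. With ρ from 25% to 100%, the absolute excess qρ(1 − δ) runs from about 1 to 11 percentage points. With ρ = 0 it is zero.

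These figures compare cases with all crackle episodes, whereas the study compares cases with all residents without pneumonia. They show direction and a plausible order of size, not an estimate for this study.

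**The case against.** Several objections have force.

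- The sign is an either/or with confusion, is one of five, and is neither necessary nor sufficient. Documented crackles are mandatory, and the article calls them rare. This limits the size of the bias but does not remove it.
- A reader might infer that crackles plus worsening disability alone make a case. That holds only if one auscultation finding counts under both the first item and criterion 2. The text permits this reading but does not state it, and the overlap exists without it.
- The sign is recorded at the episode, while the outcome is measured on separate scales at the visits. The outcome detail given for aim c concerns SPPB, a performance test that is less exposed than ADL or GIR. This stands as a limit on size.
- Events are not only reconstructed at the 6- and 12-month visits, because regular contacts with nursing-home staff are planned in between. Study staff who notice decline cannot create a case without a physician's record of crackles.
- Residents with atypical presentations may have genuine pneumonia that impairs function. Dropping them could bias the result the other way. This is a sound reason not to make a restricted set the main analysis.
- The definition is a published one adapted to nursing homes, and sign-level fields or sensitivity analyses may sit in documents not shown. However, both the definition and its use in aim c are fixed in the article, and there the overlap is not acknowledged.

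**Conclusion.** The overlap is real and partial. As written, the plan biases the functional comparison in aim c upward to the extent that events qualify only through worsening disability and that the decline persists to the next visit. Under the assumed frequencies this is about 3% to 15% of events. The true share cannot be found from the article.

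Three stronger readings are not supported.

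- That hypothesis c is true by construction: most qualifying patterns do not need the sign, and transient decline produces no bias.
- That the spurious difference is 0.1 to 0.3 ADL: this would need 10% to 30% of events to qualify through disability alone, a full ADL lost and still lost at the visit, and no decline at all in non-cases. The article gives none of these inputs.
- That the cost results are compromised: the main cost variable is total expenditure, and GIR transition is only a surrogate.

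The primary incidence aim is untouched by this point. It deserves correction because it concerns the interpretation of a secondary aim, but it is not a fundamental flaw in the study.

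**What to change.** 1. Keep the ORIG definition unchanged for primary incidence and for the main analysis of secondary aim c and tertiary aim a.
2. Record for each event which signs were met, with confusion and worsening disability as separate fields, and state whether crackles may also count as the first item of criterion 1.
3. Pre-specify, for secondary aim c and tertiary aim a, a sensitivity analysis limited to events that meet criterion 1 without the disability sign. Exclude the other events from it; do not reclassify those residents as non-cases, which would contaminate the comparison group.
4. Conclude that pneumonia worsens function only if both analyses agree, and define agreement beforehand.

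The cost is a few form fields, a short addition to the analysis plan, and fewer events in the sensitivity analysis. Because the mid-term visits were already under way, events already recorded would need some chart re-abstraction.
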